### Sample size

As this is a pilot study, a formal sample size calculation was not done [38]. This study aims to recruit 16 primary care practices (eight in NI and eight in ROI) and 20 patients per practice (*N* = 320), based on recommendations from Eldridge et al. [20] and the CONSORT guidance [21] on the minimum number of clusters required in pilot and definitive cRCTs, respectively. The aims of this pilot cRCT are to investigate feasibility and acceptability and to identify the most suitable primary outcome(s) for a definitive cluster randomised trial. The estimates from this pilot trial will be used to calculate the sample size needed using the methods outlined by Rutterford et al. [39].

Based on an assessment of the number of practices and practice sizes in the region, we will invite 50 patients per practice and, a priori, have defined a success criterion as 40% of the total number of participants invited to be recruited to the research evaluation (approximately 20 patients per practice).

### Randomisation

To limit recruitment bias and help ensure that equal numbers of patients will be recruited in both arms of the trial, randomisation of the practices to intervention or control group will take place after patient recruitment has been completed [40]. Practices will be allocated using an online system, called Sealed Envelope, by a biostatistician blinded to allocation. Practices will be allocated by minimisation according to practice size (< 4 or 4+ GPs) in the ratio 1:1.

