**Methods:**

A pilot cluster randomised controlled trial will be conducted, using a mixed-methods process evaluation to investigate the feasibility of a trial of the MyComrade intervention based on pre-defined progression criteria. A total of 16 practices will be recruited (eight in ROI; eight in NI), and four practices in each jurisdiction will be randomly allocated to intervention or control. Twenty people living with multimorbidity and prescribed ≥ 10 repeat medications will be recruited from each practice prior to practice randomisation. In intervention practices, the MyComrade intervention will be delivered by pairs of general practitioners (GPs) in ROI, and a GP and practice-based pharmacist (PBP) in NI. The GPs/GP and PBP will schedule the time to review the medications together using a checklist. Usual care will proceed in practices in the control arm. Data will be collected via electronic health records and postal questionnaires at recruitment and 4 and 8 months after randomisation. Qualitative interviews to assess the feasibility and acceptability of the intervention and explore experiences related to multimorbidity management will be conducted with a purposive sample of GPs, PBPs, practice administration staff and patients in intervention and control practices. The feasibility of conducting a health economic evaluation as part of a future definitive trial will be assessed.

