**Fig. 1 Fig1:**
[figure not shown]
MyComrade study design

A total of 16 practices will be recruited (eight in ROI; eight in NI), and four practices in each jurisdiction will be randomly allocated to the intervention or control arms. Patients with multimorbidity who are prescribed 10 or more repeat prescription medications will be identified in each practice. From each practice, 20 patients with multimorbidity will be recruited, providing a total of 320 participants. The list of 20 consented patients from each practice will be shared with participating GPs/PBPs. In the intervention arm, pairs of GPs/GP and PBPs will use the MyComrade intervention and will be asked to complete collaborative medication reviews before the 4-month follow-up time point. ROI pairs will be GP-GP, and NI pairs will be GP-PBP. Control practices will proceed with usual care. Participant data will be collected from primary care practice records and postal questionnaires sent to participants at baseline before randomisation takes place and at 4 and 8 months after the date of randomisation. Qualitative interviews to assess the study feasibility and acceptability and to explore experiences related to multimorbidity management will be conducted with a purposive sample of GPs and PBPs participating in the study, practice administration staff and patients.

A Public and Patient Involvement group has been established, involving four adults (two women and two men) from both NI and ROI and living with multimorbidity. This group have provided input into the patient recruitment materials, and qualitative interview guides, and will provide input into the interpretation of the qualitative findings and methods for disseminating the study findings. The establishment and running of this group as research partners in this study are guided by the PPI Ignite @ NUI Galway programme office, part of a national PPI programme funded by the Health Research Board in Ireland.

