### Study setting

This study will take place in primary care practices in NI and ROI. The populations of these jurisdictions are similar in terms of ethnicity, with the majority of people in both regions being white [26] and with similar socioeconomic gradients [27]. GPs in both jurisdictions work as independent contractors [28], but the health systems differ in important ways, principally that the system in ROI is a mixed public and private system, while the system in NI is publicly funded [29]. In ROI, patients are means-tested to determine eligibility for a medical card, which entitles them to GP care, medications and other medical services free at the point of access [28]. In 2019, 32.4% of the ROI population had a medical card [30]. Patients without a medical card pay out of pocket for their medical care and medications. All patients aged over 70 years get free access to GP care but only those with medical cards are eligible for free medications. In NI, GP services are free at the point of access to all patients [31].

Since 2016, most GP practices in NI have access to a PBP, although the hours and role of the PBP will vary depending on the size and specific needs of the practice. Tasks performed by the PBP may include medication reviews and medication reconciliation following discharge from the hospital [22].

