There are limitations associated with the proposed design. The study setting encompasses the whole of NI but is limited to the border region of ROI. The two settings differ in terms of characteristics such as the presence of major urban centres, which has an impact on the characteristics of GP practices that can be recruited and the number of practices available to recruit. GP practices in NI and ROI differ in a number of ways including typical practice size, often being larger in NI and practice record and medication coding systems, impacting methods of identification of eligible participants.

The overarching aim of this intervention is to optimise the management of medications prescribed for people living with multimorbidity, specifically those with prescriptions for 10 or more repeat medications. This study is an essential step in examining the potential for MyComrade to achieve this overarching aim. To gain an accurate understanding of the complex issues related to polypharmacy and medicines management in multimorbidity, and produce an effective and implementable intervention, this programme of research has been conducted closely in line with current recommendations. Therefore, this research will contribute to the evidence-base related to intervention development and feasibility testing and the management of multimorbidity in primary care nationally and internationally. The findings will be disseminated to a range of audiences, with guidance from the PPI group, including GPs, PBPs, secondary care providers and the public, through a range of media, including a dissemination event, conferences and publication.

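### 1:1 minimisation on practice size alone does not guarantee the stated four-and-four split of practices within each jurisdiction

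*Protocol article*

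**What the plan says.** The Trial design section plans 16 practices, eight per jurisdiction, and says that "four practices in each jurisdiction will be randomly allocated to the intervention or control arms". The Abstract says the same: "four practices in each jurisdiction will be randomly allocated to intervention or control". With eight practices per jurisdiction, the only reading that uses all of them is four intervention and four control in NI, and likewise in ROI.

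The Randomisation section is the only place that describes how practices are assigned: "Practices will be allocated by minimisation according to practice size (< 4 or 4+ GPs) in the ratio 1:1". It mentions neither jurisdiction nor separate runs for NI and ROI.

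Three other statements bear on the point:

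- The intervention differs by jurisdiction: "ROI pairs will be GP-GP, and NI pairs will be GP-PBP" (Trial design).
- The health systems differ: "the system in ROI is a mixed public and private system, while the system in NI is publicly funded" (Study setting).
- Size is related to jurisdiction but is not the same thing: "GP practices in NI and ROI differ in a number of ways including typical practice size, often being larger in NI" (Discussion, limitations).

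**The concern.** The design states a split by jurisdiction, and the allocation rule balances something else. Size could stand in for jurisdiction only if every larger practice were in one jurisdiction and every smaller one in the other. The article says only that NI practices are often larger.

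Three uses of the data depend on the split:

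- **Judging each version.** GP-GP review is seen only in ROI intervention practices, and GP-pharmacist review only in NI ones. The process evaluation plans one clinician interview per practice. A jurisdiction with two intervention practices instead of four would give two clinician interviews on its version instead of four.
- **The exploratory arm comparison.** If the arms hold different shares of NI and ROI practices, part of any arm difference may reflect the health system.
- **The NI/ROI comparison.** This is part of the stated aim and of the health economic subgroup analysis. It becomes less precise when one jurisdiction has few practices in one arm.

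**Working it through.** **Inputs from the article:** 16 practices, eight per jurisdiction; 1:1 ratio; one two-level balancing factor (fewer than 4 GPs, or 4 and more).

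**Assumptions, because the article does not give them:** the number of larger practices in each jurisdiction; whether the rule is deterministic or has a random element; the order in which practices are entered.

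**Step 1: size ignored.** If eight of 16 practices go to intervention without regard to jurisdiction:

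- P(4:4 in both) = C(8,4)² / C(16,8) = 4900 / 12870 = 0.381.
- P(5:3 in one, mirrored in the other) = 2 × C(8,5) × C(8,3) / C(16,8) = 6272 / 12870 = 0.487.
- P(6:2 or worse) = 1 − 0.381 − 0.487 = 0.132.

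**Step 2: size balanced exactly over all 16.** Take six larger practices in NI and two in ROI. Four of the eight larger practices go to intervention. The number of these from NI is 2, 3 or 4, with probabilities 15/70, 40/70 and 15/70. Among the eight smaller practices (two NI, six ROI), the number from NI is 0, 1 or 2, with the same probabilities. Then:

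- P(4:4 in both) = (15×15 + 40×40 + 15×15) / 70² = 2050 / 4900 = 0.418.
- P(6:2) = 2 × 15×15 / 4900 = 450 / 4900 = 0.092.

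The same calculation for other mixes gives:

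| Larger practices NI/ROI | 4:4 in both | 5:3 | 6:2 or worse |
|---|---|---|---|
| 4/4 | 0.369 | 0.483 | 0.147 |
| 5/3 | 0.378 | 0.490 | 0.133 |
| 6/2 | 0.418 | 0.490 | 0.092 |
| 7/1 | 0.500 | 0.500 | 0 |
| 8/0 | 1.000 | 0 | 0 |

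**Step 3: simulation of the rule itself** (100,000 runs per scenario). Deterministic minimisation with practices entered in random order reproduces the 4:4 column: 0.368, 0.378, 0.419, 0.500 and 1.000. If the balancing arm is chosen with probability 0.8 instead, exact 4:4 falls to 0.22–0.29 (0.56 for the 8/0 mix). If one jurisdiction is entered wholly before the other, a deterministic rule gives 4:4 with certainty when the size counts in each jurisdiction are even, and about half the time when they are odd.

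**Step 4: the same rule run separately in NI and ROI.** With five practices of one size and three of the other, each size group ends one practice out of balance, in a random direction. The jurisdiction total is 4:4 only if the two errors cancel, with probability 1/2. For both jurisdictions this is 1/2 × 1/2 = 0.25, as the simulation also shows. With even counts and a deterministic rule it is 1.

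**Step 5: candidate remedies.** Jurisdiction as a second minimisation factor gives exact 4:4 in about 0.91–0.92 of runs if deterministic (1.00 for 8/0), and 0.45–0.56 with the 0.8 random element. Allocation within each jurisdiction under a hard 4:4 constraint gives 1.00.

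**The case against.** The strongest reply is that the sections should be read together: the Trial design section places allocation within each jurisdiction, and the Randomisation section adds size as the balancing factor. The full protocol behind this condensed article may say so. That reading is possible, but the Randomisation section does not state it, and Step 4 shows that size-only minimisation within jurisdiction still does not force 4:4.

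Other parts of the reply stand and limit the point:

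- **The split is not ruled out.** A reader might infer that the stated split will not be delivered. The article does not support that: 4:4 can arise by chance, or by construction under some size mixes and entry orders.
- **Most misses are small.** A 5:3 split moves one practice per jurisdiction.
- **Arm is not confounded with version.** A reader might infer that it is. Controls receive no version, and version is tied to jurisdiction under any split, so the NI/ROI comparison mixes version with health system even at a perfect 4:4.
- **The intracluster correlation (ICC) is not specifically harmed by a skewed split.** A jurisdiction difference enters the between-practice variance under any split unless it is modelled.
- **The main progression criteria are untouched.** Practice and patient recruitment finish before randomisation, and retention is counted in total, not by arm.
- **Model covariates are commonly left to an analysis plan,** which is not shown. That jurisdiction is not named in the exploratory models is no fault here.

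**Conclusion.** The point holds as a mismatch between the stated allocation and the rule given to produce it: the four-and-four split by jurisdiction is not guaranteed. If size is balanced over all 16 practices, the chance of missing it is about 50 to 63% for the assumed mixes other than 8/0. The range depends on a size mix, degree of randomness and entry order that the article does not state.

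The consequence is a possible and partial imbalance of arm with health system, and fewer intervention practices from which to judge one version. Full confounding is very unlikely. In a pilot with feasibility outcomes, no formal sample size calculation and only tentative arm comparisons, this is a minor to moderate matter and does not have to be resolved before the trial can meet its primary objective.

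**What to change.** **If allocation is still open:** allocate separately in NI and ROI, each constrained to four intervention and four control practices, and balance size within jurisdiction as far as the constraint allows. For example, five larger and three smaller practices can be split 3 + 1 against 2 + 2. Naming jurisdiction only as a second minimisation factor is not enough (Step 5). The cost is a change in the set-up of the allocation system and one sentence in the Randomisation section.

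**If allocation has been run:** the Study status section suggests this at least in part, since recruitment was complete and introduction sessions, which follow randomisation, had gone virtual since June 2020. In that case:

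- state whether jurisdiction was a stratum;
- report the achieved number of practices by jurisdiction and arm;
- include jurisdiction and practice size as fixed effects in the exploratory mixed models, and jurisdiction in the ICC estimates.

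This costs one or two degrees of freedom at practice level, and no new data.

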### Statistical methods

#### Process evaluation and qualitative data collection and analysis

The main purpose of the process evaluation is to answer questions relating to the primary feasibility outcomes (recruitment, retention and intervention implementation). The process evaluation is informed by the approach described by Grant et al. [24] and utilises quantitative and qualitative methods across 11 framework domains (described in Table 3).

**Table 3 Tab3:** MyComrade study process evaluation framework, including implementation outcomes framework

Process evaluation framework and implementation outcomes framework		MyComrade process evaluation questions	Intervention or control	Data source to answer process evaluation question	
				Interview	Other sources
Domain					
1. Recruitment of clusters		How were practices sampled and recruited?	Both	No	Study records
		Why did practices agree to participate (or not)?	Both	GPs/PBPs Practice administrative staff	
2. Delivery to clusters		How was MC delivered to the practices?	Intervention	GPs/PBPs	Study records
3. Response of clusters		How has completing trial-related work impacted the practice? At the practice level, how is MC and related research work perceived? How has the practice been found working with the research team? Time taken to complete study activities?	Both	Practice administrative staff GPs/PBPs	
		How were patients identified/reviewed? Are they representative/is there a selection bias? Time taken to complete?	Both	Practice administrative staff GPs/PBPs	
		What were the processes involved in addressing the recruitment packs and conducting mail-outs and what was the time taken to complete?	Both	Practice administrative staff GPs/PBPs	
		What is the practice level protocol for usual care?	Control	Practice administrative staff GPs/PBPs	
4. Recruitment and reach in individuals		Who within each practice actually received the MC training? Are they representative/is there a selection bias?	Intervention	Practice administrative staff GPs/PBPs	Study records of attendance at the intervention introduction session
5. Delivery to individuals	Implementation outcomes framework 1. Fidelity	What do GPs/PBPs implement as usual care?	Control	GPs/PBPs	
		How are GPs/PBPs implementing MC? How many BCTs did pairs implement the following?	Intervention	GPs/PBPs	
		i. Plan reviews: restructuring social environment, Action planning	Intervention	GPs/PBPs	Checklist completion GP fellow calls
		ii. Conduct reviews: social support	Intervention	GPs/PBPs	Checklist completion GP fellow calls Scanned checklists to patient record
		iii. Use checklist: prompts/cues	Intervention	GPs/PBPs	Checklist completion Scanned checklists to patient record
		iv. Submit for annual appraisal or points/reimbursement: self-incentives; material incentive	Intervention	GPs/PBPs	Submission of MC activities for annual appraisal Receipt of reimbursement
6. Response of individuals	1. Acceptability 2. Adoption 3. Appropriateness 4. Feasibility	Is MC acceptable/agreeable/satisfactory to GPs/PBPs? What was GP/PBP initial intention/plan for MC? Did implementation of MC change over the course of the study (e.g. use of checklist)? Is MC compatible/relevant for general practice and multimorbidity? Is MC practical/feasible for GPs/PBPs to implement?	Intervention	GPs/PBPs	
		Has the GP/PBP ever reviewed their medication with them? How do they feel about two GPs, or GP and PBP discussing their medications without them? Did they experience any changes to their medication during the course of the study?	Both	Patients	
7. Maintenance	1. Acceptability 2. Adoption 3. Appropriateness 4. Feasibility	Has MC become integrated into practice over the course of the study? What components? Do GPs/PBPs think MC could become routine practice? Are there any opportunity costs of implementing MC?	Intervention	GPs/PBPs	
8. Unintended consequences		Were there unintended consequences, outcomes or changes in the processes?	Intervention	GPs/PBPs	
9. Theory		Proposed mechanisms of impact: How did GPs/PBPs feel about formally allocating time to review medications? Did the MC intervention help in any way in dealing with that uncertainties related to medications and considering options? Has taking part in the trial had any impact on the way GP/PBP communicates with their patients about their medications? Did GP/PBP submit details of their MC involvement as part of annual appraisal submission?	Intervention	GPs/PBPs	
10. Context		What are the differences in experiences between the NI and ROI practices in all of the framework domains, e.g.: Practice resources prescribing guidelines practice context, e.g. practice size and setting	Both	All	Practice profile questionnaire
11. Effectiveness		Did pairs complete active medication reviews? Were there changes made to the number of repeat medications prescribed (additions and de-prescribing)? Were there changes related to potentially inappropriate prescribing?	Both	GPs/PBPs	Checklist completion GP fellow calls Patient record
		Patient outcomes: Quality of life Multimorbidity treatment burden	Both	Patient	Patient questionnaires Patient record

Semi-structured interviews will be used to collect qualitative data from a purposive sample of one GP or PBP and a practice manager or administrator from each practice. From the patients recruited from each practice, one patient will be invited for an interview, through random sampling. If a patient does not respond or declines to be interviewed, a second patient will be randomly selected and invited for an interview. The topic guides will explore the experiences of those participating in the study and issues of implementation following Proctor et al.’s [41] taxonomy of implementation outcomes (acceptability, adoption, appropriateness, feasibility, fidelity, implementation cost, coverage and sustainability—see Table 3). Interviews will be conducted remotely by telephone (by EC and LH) with audio-recording and last approximately 30–60 min. Due to the geographical spread of the study, telephone interviews are most feasible, and this approach has been found to be an acceptable alternative to in-person interviews [42].

Interviews will be transcribed verbatim and analysed using the framework approach [43] in the Nvivo software. At the outset, up to six transcripts will be coded inductively by two researchers (LH and CK), who will then meet to discuss the initial coding and to agree on an analytical framework. The agreed framework will be refined inductively through subsequent rounds of coding and team discussion. Data will be summarised using a framework matrix of the themes and sub-themes through a process known as charting, which will allow data summaries to be easily generated and linked to relevant data. The two coders and a wider study team, including the PPI group, will work together to interpret the findings.

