### Intervention

The MyComrade intervention is a complex intervention, which aims to increase the behaviour of active medication review. MyComrade initially involved five components (Table 1); a sixth component material incentive was added based on the results of the first feasibility study of this intervention [19]. The intervention is described using the Template for Intervention Description and Replication (TIDieR) Checklist [33] in Additional file 2.

MyComrade will be implemented in intervention practices following recruitment of participants, baseline data collection and practice randomisation. The research team will deliver a brief introduction session on the intervention. The introduction session will be audio-recorded to allow independent fidelity assessment, in terms of content and duration. The GP research fellow with the NI- and ROI-based study teams (LMQ and SM) will contact each intervention practice 3 and 6 weeks after this session to gauge progress in terms of medication review completion and address any study-related questions.

Participating GPs and PBPs will be given the list of eligible patients from their practice who consent to take part. GP/GP and PBP pairs will schedule a time to meet each other to conduct each collaborative medication review, using a medication review checklist to guide the discussion. The medication review checklist was adapted from the “NO TEARS” tool for a medication review [34], originally designed for doctor-patient medication reviewing. This seven-item tool was selected due to its simplicity and was described by GPs in the feasibility study for the MyComrade interventions as a helpful guide for a medication review [19]. The earlier feasibility study suggested that reviews take between 10 and 30 min each. GP/PBPs will scan the completed checklist into the participant’s practice record, highlighting any potential options for medication changes and discussing these with the participant prior to making changes.

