### Outcomes

The primary outcomes are the feasibility of practice recruitment, patient recruitment, practice retention, patient retention and feasibility of intervention implementation. Secondary outcomes are completion of medication reviews (GP/PBP outcome), treatment burden and quality of life (patient outcomes) and number of prescribed medications, changes in prescribed medications, deprescribing and indicators of potentially inappropriate prescribing (prescribing outcomes). The indicators of potentially inappropriate prescribing were adapted from the set of evidence-based, validated prescribing safety indicators developed in the PINCER trial [35]. The secondary outcomes will be used to inform the choice of primary outcome should we proceed to a definitive trial at a later stage. The logic model in Additional file 4 illustrates the intervention components, proposed mechanisms of impact of each component, contextual factors and outcomes. The logic model was designed based on guidance from Moore et al. [36].

Data will be collected on GP practice demographic information and patient demographic information and healthcare utilisation. Additional file 3 provides a summary of the variables measured in this study and the data source for each. The secondary outcomes will be assessed at baseline and at 4 and 8 months after randomisation of practices. The variability, consistency, response rates, success of data collection methods and data completeness for each outcome will be determined to understand the feasibility and acceptability. These findings will help to determine the primary outcome(s) for a future definitive trial.

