#### Exploratory analysis

Linear and nonlinear mixed-effects models, which account for the cluster design and allow adjustment for baseline measurements, will be used to tentatively explore the differences in the secondary outcomes between the pilot trial arms.

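### Review completion is to be explored between arms, but two of the three non-interview sources that Table 3 lists for it exist only in intervention practices, so reviews would be detected unequally, to an unknown extent

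*Protocol article*

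**What the plan says.** - **The outcome.** The Outcomes section states: "Secondary outcomes are completion of medication reviews (GP/PBP outcome". It adds: "The secondary outcomes will be assessed at baseline and at 4 and 8 months after randomisation of practices". The same section says that the secondary outcomes will help to pick the primary outcome of a definitive trial.
- **The comparison.** Under Exploratory analysis, mixed-effects models with adjustment for baseline "will be used to tentatively explore the differences in the secondary outcomes between the pilot trial arms".
- **The sources.** In Table 3, domain 11 (Effectiveness), the row that opens with "Did pairs complete active medication reviews" is marked as applying to both arms. Its non-interview sources are "Checklist completion GP fellow calls Patient record", and GP/PBP interviews are listed beside them.
- **Where those sources exist.** The Intervention section makes the checklist part of the collaborative review. It also says that the GP research fellow "will contact each intervention practice 3 and 6 weeks after this session to gauge progress in terms of medication review completion".
- **Who works in pairs.** Under Trial design: "In the intervention arm, pairs of GPs/GP and PBPs will use the MyComrade intervention and will be asked to complete collaborative medication reviews". Control practices continue with usual care.

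**The concern.** An outcome compared between arms should be found with the same chance in each. Here two of the three non-interview sources can add reviews in one arm only. A usual-care review in a control practice is counted only if the patient record shows it, whereas an intervention review has further routes to being counted.

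Control practices may well have reviews to miss. The Introduction gives NI practice pharmacists a key responsibility for medication reviews, and Study setting lists reviews among the tasks that they may perform. The question also speaks of pairs, a way of working that only intervention practices are asked to adopt, so its wording does not carry over to usual care.

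Review completion is also among the outcomes whose variability the pilot will estimate, and the pilot data feed the number of clusters and the intracluster correlation for the next trial. A contrast that is too large and a control rate that is too low could make this outcome look a better primary outcome than it is, and could distort a sample size built on it.

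**Working it through.** The plan states no figure for this point, so there is none to reproduce. The check first sets the passages side by side and then shows the possible size on assumed values.

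**Step 1. Which sources exist in which arm**

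| Source in domain 11 | Intervention | Control | Basis |
|---|---|---|---|
| Checklist completion | yes | none described | Intervention section; Table 3 domain 5 rows using it are marked intervention only |
| GP fellow calls | yes | none described | Intervention section; Table 3 domain 5, likewise |
| Patient record | yes, including the scanned checklist | yes | Intervention section; quantitative data collection |
| GP/PBP interview | yes | yes | one GP or PBP per practice, so no completion status for each patient |

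Domain 11 therefore reuses, for both arms, sources that domain 5 of the same table restricts to one arm.

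**Step 2. Effect of counting a review if any source shows it**

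Assumed inputs, none from the documents: true completion p, the same in both arms; record sensitivity s_R; combined sensitivity of checklist and calls s_X. Sources are taken as independent, with no false positives.

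- Control detection: s_C = s_R
- Intervention detection: s_I = 1 − (1 − s_R)(1 − s_X)
- Spurious difference: D = p(s_I − s_C) = p(1 − s_R)s_X

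With p = 0.40 and s_X = 0.80:

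- s_R = 0.5: 0.40 × 0.5 × 0.80 = 0.160
- s_R = 0.7: 0.40 × 0.3 × 0.80 = 0.096
- s_R = 0.9: 0.40 × 0.1 × 0.80 = 0.032

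Over p = 0.2 to 0.6, s_R = 0.5 to 0.9 and s_X = 0.5 to 0.95:

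- Smallest: 0.2 × 0.1 × 0.5 = 0.010
- Largest: 0.6 × 0.5 × 0.95 = 0.285

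One source of equal sensitivity in both arms gives D = 0.

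**Step 3. When the arms truly differ**

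Take completion of 0.80 against 0.40 (true difference 0.40), s_R = 0.7 and s_X = 0.95. Then s_I = 1 − 0.3 × 0.05 = 0.985.

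- All sources: 0.80 × 0.985 − 0.40 × 0.7 = 0.508
- Record only, equal sensitivity: (0.80 − 0.40) × 0.7 = 0.280

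The arm-specific sources add 0.508 − 0.280 = 0.228 to what equal detection would show. A common but imperfect source understates the true difference, but treats the arms alike.

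**Step 4. What record-only extraction leaves behind**

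Intervention practices scan the checklist into the record, and Table 1 lists €50/£43 per completed review for intervention practices only. If record sensitivity were 0.9 in the intervention arm and 0.7 in control, with p = 0.40 in both, the record alone would still give 0.40 × (0.9 − 0.7) = 0.08. Moving to the record reduces the unequal detection but does not remove it.

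**The case against.** The strongest reply is that Table 3 is a process-evaluation framework and not the outcome definition. The Outcomes section says that Additional file 3 gives the data source for each variable. That file is not shown and may name one source for review completion. The domain 11 cell also serves three questions, so checklists and calls may be meant for intervention pairs and the patient record for both arms. Assessment at baseline, before any checklist or call exists, points to the record too. The comparison is tentative, review completion is not a progression criterion in Table 2, and the pilot will itself examine how well its data collection worked.

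Much of this stands. It limits the weight of the point and leaves the actual outcome definition open. It does not clear Table 3, which marks the row for both arms without saying which source serves which question. If Additional file 3 names a single source, the table still has to be aligned with it. If baseline comes from the record and follow-up from all sources, the baseline adjustment uses a different measure from the one modelled in the intervention arm.

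A reader might go further and infer that the control rate is zero by construction, that a logistic mixed model could not estimate the contrast, or that the whole control rate would be lost. Those readings need a definition by checklist alone, or one that counts only reviews by a pair. The documents state neither: the patient record is in the same cell, and the Outcomes section speaks of medication reviews without requiring a pair.

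**Conclusion.** The point holds in limited form. Followed as written, domain 11 would detect reviews more fully in the intervention arm and tilt an exploratory contrast towards it. This affects review completion only, since the two prescribing questions in the same row can be answered from the record in both arms.

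The size cannot be determined from the documents. The range of 1.0 to 28.5 percentage points rests wholly on assumed rates, assumed sensitivities and independent sources, and it is close to zero if the record captures nearly every review in both arms. The direction is relative to equal detection. When the arms truly differ, imperfect detection also attenuates, so the net error against the truth depends on both effects.

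This should be corrected because the outcome may inform the choice of primary outcome. It does not threaten the pilot's feasibility conclusions.

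**What to change.** 1. For the between-arm outcome, define completion in terms that fit both arms: any medication review documented in the practice record, whether or not a pair did it.
2. Have the research nurses extract it with the same tool and rule in both arms at baseline, 4 and 8 months.
3. Align Table 3, domain 11 and Additional file 3 with this definition.
4. Keep checklist completion and fellow calls as intervention-arm fidelity measures, outside the arm comparison.
5. Report the contrast with and without reviews evidenced only by a scanned MyComrade checklist. The second analysis will drop some genuine reviews, so the pair shows how far the contrast depends on the form and is not a correction.
6. State the remaining recording difference as a limitation when this outcome is considered for the definitive trial.

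The cost is one definition, one field in the existing record-extraction tool with a marker for scanned-checklist-only evidence, and one extra exploratory analysis. Free-text notes may under-record reviews in both arms, which lowers the observed rates.
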